#### Variable selection

At the time of writing, a failsafe model selection strategy on which all statisticians and other experts in diagnostic and predictive modeling agree does not appear to exist. However, in his book 'Regression modeling strategies (2001)'[62], Harrell made some general proposals for researchers to tailor to the specific circumstances. We intend to use penalized logistic regression, and Tibshirani's *lasso *(least absolute shrinkage and selection operator)[63] in particular to combine the requirements of counteracting over-optimism (shrinkage of regression coefficients) while leaving the opportunity that some coefficients are set to zero, which serves the requirement of a parsimonious model. Bootstrapping will be used to estimate the penalization coefficient.[62] As a form of sensitivity analysis, we shall also explore bootstrapped stepwise regression[64,65] to see how well these approaches concur. We will avoid univariable preselection of predictors. The linearity assumption will be checked for all continuous predictors.

Discrimination of the model(s) will be visualized in high resolution histograms and summarized as 5^th^, 10^th^, 25^th ^50^th^, 75^th^, 90^th^, and 95^th ^centiles of these, Brier score and the area under the receiver operating characteristics curve (ROC) with 95% confidence intervals (overall discrimination).[66]

Using the regression coefficients of the independent diagnostic indicators, an easy to use, multivariable diagnostic rule (clinical index) will be derived, consisting of relevant tests and their diagnostic values.

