**Methods:**

Women who contact their GP with painful and/or frequent micturition undergo a series of possibly relevant tests, consisting of patient history questions and laboratory investigations. Using urine culture as the reference standard, two multivariable models (diagnostic indices) will be generated: a model which assumes that patients attend the GP surgery and a model based on telephone contact only. Models will be made more robust using the bootstrap. Discrimination will be visualized in high resolution histograms of the posterior UTI probabilities and summarized as 5^th^, 10^th^, 25^th ^50^th^, 75^th^, 90^th^, and 95^th ^centiles of these, Brier score and the area under the receiver operating characteristics curve (ROC) with 95% confidence intervals. Using the regression coefficients of the independent diagnostic indicators, a diagnostic rule will be derived, consisting of an efficient set of tests and their diagnostic values.

The course of the presenting complaints is studied using 7-day patient diaries. To learn more about the natural history of UTIs, patients will be offered the opportunity to postpone the use of antibiotics.

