### Diagnostic work-up

Diagnosis of UTIs in general practice consists of various medical history questions and laboratory investigations, of which nitrite and leukocyte esterase (LE) dipstick tests, microscopic examination of urinary sediment, and dipslide are the ones most widely used.

Most diagnostic tests for UTIs have been studied before in single-test evaluations, implying that a test is compared to the urine culture, not taking into account the distribution of other test results in the population studied. [17-19] In practice, however, the diagnostic work-up is inherently multivariable, and test results are mutually dependent. [20-36] Therefore it cannot be generally expected that a test's sensitivity is invariant over different degrees of prior testing. For example, the sensitivity of the nitrite dipstick test will be affected by the information contained in the diagnostic profile resulting from prior test results.[37]

The primary objective of the Amsterdam Cystitis/Urinary Tract Infection Study (ACUTIS) is to determine the (additional) diagnostic value of relevant tests from patient history and laboratory investigations, taking into account their mutual dependencies. Next, an easy to use, multivariable diagnostic rule (clinical index) will be derived. After suitable (external) validation, GPs may use the (validated) rule to estimate UTI probabilities for women with different combinations of test results.

Little et al. and McIsaac et al. described similar work in a UK and a Canadian population, respectively.[38,39] However, different inclusion criteria were used (see further) and urine samples were transported as in routine practice before cultures were made, whereas in ACUTIS, to assure reliability of the cultures (= reference standard), urine samples are being refrigerated until being cultured. Furthermore, both earlier studies did not assess diagnostic values of the sediment and dipslide investigations.

Other similar studies.[40,41] were performed before the European Urinalysis Guidelines.[42] recommended a cut-off value of 10^3 ^cfu/ml for significant *Escherichia coli *bacteriuria and therefore only used the traditional cut-off value of 10^5 ^cfu/ml. Besides, they did not assess dipstick investigations and/or were not performed in a primary care setting.[41]

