### Variable selection strategy

#### General objectives

We aim to generate two models (diagnostic indices). First, a model which assumes that patients attend the GP surgery. Second, a model based on telephone contact only, since in daily routine this is very often the first and only contact with the patient.

Finally, using different threshold probabilities for 'no further action' (e.g. advice to increase the intake of water, 'wait and see') and prescription of an antibiotic, respectively, we will develop a diagnostic test algorithm such that patients may undergo the least number of possible tests. That is, if, regardless of its results, a certain test can be shown not to take a patient across one of the abovementioned thresholds for specific clinical action, that test may be informative, but not sufficiently so to change management. Therefore it is superfluous. It is possible that a 'telephone only' model provides sufficient certainty for patients with specific combinations of patient history items, while for other patients urinalysis at the GP surgery is needed to decide on management correctly.

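### The models are judged only by measures labelled as discrimination, with no stated optimism correction and no calibration plot, slope or intercept, although absolute probability thresholds decide which tests are dropped

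*Protocol article*

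**What the plan says.** The Variable selection section of the protocol article sets out the evaluation in some detail. It opens with "Discrimination of the model(s) will be visualized in high resolution histograms and summarized as" seven named centiles, and continues with "Brier score and the area under the receiver operating characteristics curve (ROC) with 95% confidence intervals (overall discrimination"). The abstract's Methods repeats the list.

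The protection against overfitting is the lasso, chosen "to combine the requirements of counteracting over-optimism (shrinkage of regression coefficients") together with parsimony.

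The bootstrap has three stated roles:
- tuning: "Bootstrapping will be used to estimate the penalization coefficient" (Variable selection);
- a sensitivity analysis: "we shall also explore bootstrapped stepwise regression" (same section);
- a general aim: "Models will be made more robust using the bootstrap" (abstract, Methods).

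The intended product works with absolute risk. The General objectives section plans a test algorithm "using different threshold probabilities for 'no further action"' and for antibiotic prescription, and drops any test whose result cannot carry a woman across one of them. The Diagnostic work-up section says, on condition of external validation, that "GPs may use the (validated) rule to estimate UTI probabilities for women with different combinations of test results". The abstract's Discussion makes validation a preference. No second data set is planned within the study.

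**The concern.** Two separate properties are at issue.

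**Optimism.** When the same women are used to tune the penalty, select predictors, fit the model and compute AUC and Brier score, those figures are on average better than the model will achieve in new women. Shrinking the coefficients makes the model itself less extreme. It does not turn an apparent AUC into an estimate of performance in new women, and a confidence interval around an apparent AUC is centred too high.

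**Calibration.** A threshold rule asks whether a predicted risk of, say, 0.20 corresponds to an observed risk near 0.20. AUC depends only on ranking, and histograms and centiles describe only the predictions. The Brier score responds to calibration but mixes it with discrimination in one average over all women. The plan then derives an easy-to-use index from the coefficients. Any simplification can change the probabilities again, and no check of that index is named.

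At stake are the accuracy figures first published for the surgery and telephone models, and the decision about which tests count as superfluous.

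**Working it through.** **1. Inputs.** The Sample size section gives 15 candidate indicators, some modelled as dummies, about 200 women with a UTI, and prevalence 40–60%. The plan's range reproduces: 200/0.6 = 333 and 200/0.4 = 500. At an assumed 10 events per parameter, 200/10 = 20 parameters. The article gives no expected AUC, Brier score, predictor effects or threshold values, so the rest is illustrative.

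**2. Residual optimism after the lasso.** Assumptions: 20 correlated binary predictors, 6 with an effect; prevalence about 50%, hence about 0.5 × 333 = 167 or 0.5 × 500 = 250 events, bracketing the planned 200; penalty chosen by bootstrap out-of-bag deviance; 50 runs per setting; performance in 20,000 new patients. Optimism is apparent minus new-patient AUC, and new-patient minus apparent Brier.

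| Effects, N | Lasso AUC, apparent / new | Optimism | Lasso Brier, apparent / new | Optimism | Lasso slope in new patients | Unpenalised AUC optimism |
|---|---|---|---|---|---|---|
| weaker, 333 | 0.775 / 0.742 | 0.033 | 0.196 / 0.209 | 0.013 | 1.22 | 0.791 − 0.727 = 0.064 |
| weaker, 500 | 0.768 / 0.747 | 0.021 | 0.198 / 0.206 | 0.008 | 1.22 | 0.779 − 0.737 = 0.042 |
| stronger, 333 | 0.842 / 0.825 | 0.017 | 0.164 / 0.173 | 0.009 | 1.27 | 0.853 − 0.816 = 0.037 |
| stronger, 500 | 0.840 / 0.829 | 0.011 | 0.164 / 0.170 | 0.006 | 1.19 | 0.847 − 0.823 = 0.024 |

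The lasso removes about half of the AUC optimism of an unpenalised model (0.033/0.064 = 0.52; 0.011/0.024 = 0.46) and leaves the rest.

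**3. Calibration after the lasso.** A mean slope of 1.19 to 1.27 means predictions too close to the average. If the intercept is zero, observed risk at a predicted 0.20 is 1/(1 + 4^slope), because the odds at 0.20 are 1 to 4. This gives 1/(1 + 4^1.19) = 0.16 and 1/(1 + 4^1.27) = 0.15. Shrinkage does not by itself guarantee calibrated risks.

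**4. What one Brier score can show.** Let the true log-odds be normal with mean 0 and SD 1.3, and let the model report log-odds multiplied by s. Ranking, and so AUC, is identical for every s. At a predicted 0.20 the reported log-odds are ln(0.25) = −1.386, so the true log-odds are −1.386/s.

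| s | Brier score (one million simulated records) | True risk at predicted 0.20 |
|---|---|---|
| 1 | 0.1885 | 0.20 |
| 1.5 | 0.1930 | 1/(1 + e^0.924) = 0.28 |
| 0.6 | 0.1945 | 1/(1 + e^2.310) = 0.09 |

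The simulated observed risks in a narrow band around 0.20 were 0.20, 0.29 and 0.09, in line with the formula up to sampling error. Brier changes by 0.0045 and 0.0060, less than its optimism in most rows of step 2. These distortions equal calibration slopes of 1/1.5 = 0.67 and 1/0.6 = 1.67. They are stress tests, stronger than the average lasso result in step 2.

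**The case against.** The strongest reply is that a journal article condenses the plan, and that bootstrap correction and calibration plots belong in a fuller document that is not shown. The text never says that AUC and Brier will be uncorrected, the abstract promises robustness through the bootstrap, the lasso was chosen to counter over-optimism, and external validation is foreseen before use.

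Much of this stands, and it limits the point. Several stronger readings are tempting but not supported:

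- **That the reported accuracy will be optimistic.** Use of uncorrected values from the development data is an inference, reasonable because no other data set is planned. What can be said is that no correction is stated.
- **That calibration is not measured at all.** The Brier score has a calibration component; it is a weak check, not an absent one.
- **That the optimism rivals the sampling error.** The illustrative 0.011 to 0.033 lies below an AUC confidence half-width of about 0.04 to 0.05 at this size. The larger values belong to an unpenalised model, which is not the main analysis.
- **That the telephone-only rule will be overstated.** The article offers this only as a possibility, and the direction is open. Predictions pulled towards the average put fewer women beyond a threshold on history alone, but also make it harder for a further test to carry a woman across one.

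What the reply does not remove is that the article did not simply defer the evaluation. It fixes a list down to seven centiles and labels all of it discrimination. It gives the bootstrap three roles, none of them correction of performance. Validation after the study does not protect the study's own published figures.

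**Conclusion.** The point holds as a cheap improvement. Followed as written, the plan would yield AUC and Brier values with residual optimism that shrinkage does not remove, and a threshold algorithm checked for calibration only through one Brier score. The illustrative size at N = 333 and 500 is about 0.01 to 0.03 in AUC and 0.006 to 0.013 in Brier. These figures depend on assumed predictor effects and a prevalence of about 50%; they are not estimates for this study. The calibration half is the stronger one: it rests on the plan's own use of absolute thresholds, and on the fact that AUC cannot register a change of slope and the Brier score registers it only faintly.

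**What to change.** State in the analysis plan that the whole modelling procedure (imputation, penalty tuning, selection and derivation of the score) will be repeated in each bootstrap sample, and report optimism-corrected AUC and Brier score. Add the calibration intercept, slope and curve for the surgery model, the telephone model and the simplified index, with observed against predicted risk around whatever action thresholds the investigators adopt. Describe the Brier score as overall accuracy, not discrimination.

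The cost is analysis time only: no new data are needed and bootstrapping is already planned. The reported AUC may be slightly lower.

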## Substudies

### Prognosis

Using our diagnostic rule, the probability of a positive culture at baseline can be estimated. For a clinician it may also be relevant to learn more about a patient's prognosis and how this is affected by antibiotic medication. In previous studies 25 to 50% of women presenting with UTI symptoms and/or bacteriuria have been reported to recover spontaneously within one week. [43-45] It would be useful to know whether these patients, for whom antibiotics are not indicated, can be identified at baseline based on their clinical profiles.

In ACUTIS, all patients are asked to record their symptoms and possible antibiotic use in a special diary for 7 days. To learn more about the natural course of UTI, we will offer eligible women the opportunity to postpone the use of antibiotics. For patients who have not used antibiotics after 7 days, we shall try to secure a second urine specimen for culture. As a result, two prognostic models may be developed, with clinical and bacteriological cure after one week serving as dependent variables, respectively. Regression analysis will be used to assess the effects of antibiotic treatment using all cogent potential confounders to counteract possible confounding by indication as much as possible. If in specific subdomains of women no effect of antibiotics is found, randomised trials may be indicated to confirm such findings. If, on the other hand, an effect is found, the effect may be non-existent in particular subgroups. However, the power to detect such subgroup effects (or a lack of it) is probably somewhat limited. Women with milder symptoms may be more likely to defer antibiotics. We consider this not to be a great problem, since this is the subdomain of patients in which doubt about the value of antibiotics is greatest. Placebo-controlled randomized clinical trials in the subdomain of patients with severe dysuria and/or frequency are likely to incur ethical problems. If our results are promising, however, an RCT may be performed in the future (possibly by using a delayed prescription approach. [67-69]).

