### Prognosis and natural history

Placebo arms of randomized controlled trials suggest that 25 to 50% of women presenting with a combination of UTI-symptoms and bacteriuria will have recovered in one week without using antibiotics. [43-45] Using data from ACUTIS, we will try to make a prognostic index. Using the prognostic index, a GP can estimate the 7-day course for women with different combinations of test results and decide which women are most likely to benefit from antibiotic treatment.

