### Clinical assessments (see table 1)

**Table 1 T1:** Assessment schedule

	**GP or GP assistant**	**Patient**
**day 1 (baseline)**	Check availability	
	Obtain informed consent	
		Collect urine at GP surgery
	Perform dipstick and dipslide (and optionally sediment)	Fill in questionnaire
	Send urine to laboratory (refrigerated) for culture and sediment	

**day 2**	Examine dipslide	

**day 1 till day 7**		Record symptoms in diary

**day 8**	If patient did not use antibiotic: collect urine and send for culture	

After eligibility has been confirmed and informed consent has been obtained, urine is collected in a sterile container. Instructions for the collection method may be given at the GP's discretion, but are not necessary, as they have been reported to have no consequences for the extent of contamination. [50-52] We insist that the urine sample is collected at the GP surgery, since collection at home will cause at least some specimens to remain non-refrigerated for too long, thus rendering urinalysis unreliable.[53]

After urine collection, patients are asked to fill in a detailed questionnaire to record presence and severity of signs and symptoms (see additional file 1). Furthermore, they are given a special diary, in which they are to record clinical symptoms and any use of antibiotics for 7 days.

The GP or GP assistant performs a dipstick test (Multistix^® ^5, Siemens Medical Solutions Diagnostics™) and a dipslide test (Uricult^® ^classic, Orion diagnostica™). Dipsticks will be assessed automatically by a Clinitek Status^® ^analyzer (Siemens Medical Solutions Diagnostics™) to reduce inter-observer variation.

Immediately after dipstick and dipslide investigations have been performed, urine samples are stored in a refrigerator at the GP surgery. Within 8 hours they are transported to two laboratories (see below) at 4°C by a specialized courier service.

GPs are free to perform a urinary sediment investigation, the results of which will then be documented. However, in the statistical analysis we will assess the diagnostic value of the urinary sediment investigation performed by experts at the Laboratory for Clinical Chemistry of the Academic Medical Center in Amsterdam. Only if the sediment investigation proves to be useful under the optimal conditions of the laboratory, we will repeat it under daily practice conditions in a sub-study to be carried out after the main study has been completed (see further).

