## Discussion

Whereas most previous studies on diagnosis of UTIs are single-test evaluations, we will perform a multivariable analysis and develop an easy to use diagnostic rule for general practice. This will allow efficient diagnosis of UTIs, using only those diagnostic indicators which have proven added value to rule in or rule out UTI. For a large number of women with painful and/or frequent micturition, additional urine investigations might prove to add no useful information to what is already known from specific patient history questions.

This implies that in these cases the diagnostic procedure can be completed by telephone, which makes life easier for GP and patient alike. Another possibility is that patients, before contacting their GP, use a simplified questionnaire (based on the study results), available e.g. from the Internet or from their GP's office. As a result, the diagnostic work-up will be more cost-effective and less time-consuming. Besides, since use of dipslide and culture might be reduced, there may be less time delay in UTI diagnosis.

In sub-studies we will try to extend our diagnostic rule to diagnosis of *Chlamydia trachomatis *or *Neisseria gonorrhoeae*. Furthermore, prognostic indicators (potentially including antibiotics) of the 7-day course of painful and/or frequent micturition will be assessed in our cohort study.

We expect to be able to submit the first results of ACUTIS no later than by the end of 2009.

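### The prognosis substudy promises the 7-day course and who benefits from antibiotics, but its only named outcomes are cure after one week, which cannot register recovery that comes sooner within the week

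*Protocol article*

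**What the plan says.** **The aim.** Under Prognosis and natural history (Background), the article says: "Using the prognostic index, a GP can estimate the 7-day course for women with different combinations of test results". The same sentence adds that the GP can "decide which women are most likely to benefit from antibiotic treatment". The Discussion returns to the course: "prognostic indicators (potentially including antibiotics) of the 7-day course of painful and/or frequent micturition will be assessed in our cohort study".

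**The outcomes.** Under Substudies, Prognosis: "two prognostic models may be developed, with clinical and bacteriological cure after one week serving as dependent variables, respectively". No time-to-recovery, daily-score or repeated-measures outcome is named.

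**The data.** Under Clinical assessments, patients receive a diary "in which they are to record clinical symptoms and any use of antibiotics for 7 days". Table 1 schedules it from day 1 to day 7.

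**The rationale.** After citing 25 to 50% spontaneous recovery within one week, the Prognosis section says of those who recover: "It would be useful to know whether these patients, for whom antibiotics are not indicated, can be identified at baseline based on their clinical profiles". It expects women with milder symptoms to be likelier to defer antibiotics. It treats a subdomain with no antibiotic effect as a possible reason for randomised trials.

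**The concern.** A status at one week is not a course. A model of it yields one probability per woman, at one time. It says nothing about whether she is well on day 2 or day 7, which is part of what the Background promises the GP.

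The same limit touches the question of benefit. A woman who would be well on day 6 untreated and on day 3 treated counts as cured either way, so the planned outcome gives her no benefit. The rationale sentence already describes women who recover within the week as not needing antibiotics, which presupposes an answer to what the substudy sets out to assess.

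At stake is whether a finding of no effect on one-week cure could be taken as no benefit when symptom days are in fact being saved. The risk is greatest where most women recover quickly, and that could include the milder women expected to defer.

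**Working it through.** **1. Stated sample size.** The Sample size section needs about 200 women with a UTI at a UTI probability of 40 to 60%: 200/0.60 = 333 and 200/0.40 = 500. Both match the printed range. These figures size the diagnostic model; none is given for the prognostic models.

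**2. What one-week cure cannot register.** With 25 to 50% recovering untreated (Prognosis section), the women who would be cured by day 7 without antibiotics number:
- of 333: 0.25 × 333 = 83 to 0.50 × 333 = 167;
- of 500: 125 to 250.

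For those also cured by day 7 under treatment, the difference in one-week cure is zero whatever the timing. Suppose they recover on day 6 untreated and day 3 treated (assumed days). The day-7 difference is 0, the day-3 difference is 25 to 50 percentage points, and mean symptomatic time over the whole group falls by 0.25 × 3 = 0.75 to 0.50 × 3 = 1.5 days.

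**3. How much power is lost.** Assumptions, none from the article: exponential recovery, 50 women per group, treatment from day 0, no confounding, two-sided 5%.
- Recovered by day t: 1 − exp(−ln 2 × t / median). Equivalently, treated cure p1 = 1 − (1 − p0)^RR, with p0 the untreated cure and RR the recovery rate ratio.
- Power for day-7 cure: Φ[(p1 − p0)/SE − 1.96], SE = √{[p0(1 − p0) + p1(1 − p1)]/50}.
- Power for time to recovery (log-rank): Φ[√(D/4) × ln RR − 1.96], D = 50(p0 + p1).

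Within the protocol's own 25 to 50%:

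| Untreated cure, day 7 | RR | Treated cure, day 7 | Power, day-7 cure | Power, time to recovery |
|---|---|---|---|---|
| 25% | 1.5 | 35% | 19.6% | 19.8% |
| 25% | 2 | 44% | 52.1% | 52.9% |
| 50% | 1.5 | 65% | 32.2% | 33.5% |
| 50% | 2 | 75% | 76.2% | 78.2% |

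The loss is about 0 to 2 points. Medians of 7 v 4 days (50% v 70% cured) agree: 56% v 58%.

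In fast-recovering subgroups (rates assumed):

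| Medians, untreated v treated | Cured by day 7 | Recovered by day 3 | Power, day-7 cure | Power, time to recovery |
|---|---|---|---|---|
| 2 v 1.2 days | 91% v 98% | 65% v 82% | 36% | 70% |
| 2.5 v 1.5 days | 86% v 96% | 56% v 75% | 45% | 68% |

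First row in full: SE = √[(0.9116 × 0.0884 + 0.9825 × 0.0175)/50] = 0.0442; (0.9825 − 0.9116)/0.0442 = 1.60; Φ(1.60 − 1.96) = 36%. D = 50 × (0.9116 + 0.9825) = 94.7; √(94.7/4) × ln(2/1.2) = 2.49; Φ(2.49 − 1.96) = 70%.

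**4. Which outcome carries the antibiotic comparison.** The second culture is sought only from women who have used no antibiotics, so bacteriological cure cannot compare treated with untreated women. Of the two named outcomes, only clinical cure after one week can.

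**The case against.** The strongest reply is that the damaging scenarios lie outside the documents' range. They need 86 to 91% untreated recovery by day 7, the article reports 25 to 50%, and within that range almost no power is lost. This stands, and it limits the size of the point. A reader might infer that any faster recovery within the week is invisible to the planned models. The documents do not support that: at a rate ratio of 2, one-week cure would rise from 25% to 44%, or from 50% to 75%. The effect is fully hidden only for women cured by day 7 either way.

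The substudy is also exploratory. The models may be developed, subgroup power is acknowledged to be limited, and a null finding in a subdomain is a lead for a randomised trial, not a treatment rule. That softens the consequence, but a confirmatory trial does not make the cohort outcome register days gained.

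Third, a condensed article may leave outcome detail to the full protocol. Here, however, it names both the aim and the dependent variables, and they do not match. That the outcome is yes/no, and that the antibiotic regression uses it, are the natural readings and not explicit statements.

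Finally, a plain time-to-recovery model would bring its own bias. Women may postpone antibiotics and start during the week, and early recoverers never start. With antibiotic use as a fixed covariate, waiting time before the start would be credited to treatment (immortal-time bias). This stands and shapes the fix.

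**Conclusion.** The mismatch between the promised 7-day course and the modelled one-week status is in the text and holds at any recovery rate. The stated outcomes cannot deliver the course, and they assign zero benefit to every woman cured by day 7 under either management.

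The effect on power is conditional. It is negligible at the protocol's overall 25 to 50% untreated recovery. It is material only where most women recover quickly, such as 36% v 70% at about 91% untreated recovery. Whether the milder women form such a subgroup is an assumption. These power figures also rest on exponential recovery, 50 per group, immediate treatment and no confounding.

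The point is modest but worth acting on, because the data needed are already being collected.

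**What to change.** 1. Add diary-recorded time to recovery, or the daily symptom course, censored at the last diary day, as a clinical dependent variable of both the prognostic model and the antibiotic comparison.
2. Enter antibiotic start as time-dependent, using the start recorded in the diary, and state how symptoms that return after a symptom-free day are handled.
3. Keep one-week cure alongside, and state that no effect on one-week cure alone will not be read as no benefit.
4. Reconcile the Prognosis sentence on women who recover within one week ("It would be useful to know whether these patients, for whom antibiotics are not indicated, can be identified at baseline") with the substudy's aim of assessing that benefit. This is a request for consistency, not a view on who should be treated.

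Cost: somewhat more analysis work, mainly the time-dependent treatment model. No new data collection is needed.

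### The reason given for accepting that milder cases may defer antibiotics more often covers milder women only, while the intended use of the prognostic index has no severity limit

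*Protocol article*

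**What the plan says.** Two sections of the protocol article bear on this.

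**Background, Prognosis and natural history.** The aim is worded as an attempt: "Using data from ACUTIS, we will try to make a prognostic index". The index is meant to let a GP estimate the one-week course for women with differing combinations of test results and "decide which women are most likely to benefit from antibiotic treatment". No severity limit is placed on that use.

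**Substudies, Prognosis.** The untreated group arises by choice: "we will offer eligible women the opportunity to postpone the use of antibiotics". The antibiotic effect is to be estimated by regression, "using all cogent potential confounders to counteract possible confounding by indication as much as possible". On selection by severity the article states: "Women with milder symptoms may be more likely to defer antibiotics. We consider this not to be a great problem", the reason being "since this is the subdomain of patients in which doubt about the value of antibiotics is greatest". It also grants that "the power to detect such subgroup effects (or a lack of it) is probably somewhat limited", and adds: "If in specific subdomains of women no effect of antibiotics is found, randomised trials may be indicated to confirm such findings". It expects ethical difficulty with placebo-controlled trials in women with severe dysuria or frequency.

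The article states no expected number of deferring women, overall or by severity, and no share of severe cases. Its only sample size is for the diagnostic model.

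**The concern.** The reason offered for accepting the selection is sound for a result confined to milder women. It does not carry over to an index meant for women across the range of profiles, because the selection would thin out the untreated group exactly where that reason does not apply.

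To say who benefits, the model needs both the treated and the untreated course at a given profile. Adjustment for measured confounders works where treated and untreated women share profiles. Where few untreated women have severe symptoms, the model fills in their untreated course from the milder women, through whatever linearity and additivity it assumes. The regression output does not by itself show which predictions are supported by data and which are extrapolated.

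At stake is a GP reading an untreated prognosis, or an absence of antibiotic benefit, for a severe profile that hardly any untreated woman in the cohort had. This follows from selection at baseline alone.

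**Working it through.** **1. The plan's own figure.** The diagnostic study needs about 200 women with a UTI, at an assumed UTI probability of 40–60%: 200/0.60 = 333 and 200/0.40 = 500. The stated range of 333 to 500 women reproduces. It was not derived for the prognosis substudy, but it is the cohort from which deferring women come.

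**2. Inputs.**
- From the article: N = 500 (upper end, the more favourable case); recovery without antibiotics at one week, 25 to 50%, midpoint p = 0.375.
- Assumed, because the article gives no value: share with severe symptoms s = 30%; overall deferral D = 10 to 50%; odds ratio of deferral, severe versus milder, OR = 0.25 or 0.5.

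**3. Formulas.** With m and v the deferral probabilities in milder and severe women, solve
- s·v + (1 − s)·m = D, and
- v/(1 − v) = OR · m/(1 − m).

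Untreated severe women: n = N·s·v. The 95% half-width of a raw recovery proportion is 1.96·√(p(1 − p)/n).

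**4. Results, N = 500, 30% severe (150 women).**

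| D | OR | m | v | n = 150·v | Half-width |
|---|---|---|---|---|---|
| 10% | 0.25 | 0.128 | 0.035 | about 5 | about ±41 points |
| 20% | 0.25 | 0.252 | 0.078 | about 12 | about ±28 points |
| 35% | 0.25 | 0.432 | 0.160 | about 24 | about ±19 points |
| 50% | 0.5 | 0.551 | 0.381 | about 57 | about ±13 points |

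Check of the second row: 0.3 × 0.078 + 0.7 × 0.252 = 0.200; n = 150 × 0.0778 = 11.7; 1.96·√(0.375 × 0.625/11.7) = 0.28. In the first row the normal approximation is poor, and the half-width says only that the data are uninformative.

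For comparison, the second row leaves 350 × 0.252 = 88 untreated milder women, with a half-width of 1.96·√(0.234/88) = 0.10, about ±10 points.

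**5. Wider range.** With N from 333 to 500, severe share from 30 to 50%, D from 10 to 50% and OR from 0.1 to 1, n runs from about 2 (N = 333, 30% severe, D = 10%, OR = 0.1) to 125 (N = 500, 50% severe, D = 50%, OR = 1, that is, no selection).

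**6. Reading.** The cited recovery range of 25 to 50% is 25 points wide. An interval of ±19 to ±28 points spans 38 to 56 points in all, more than that range; ±13 points spans about as much as the range. These half-widths describe raw proportions. They show how thin the direct data could be, and hence how much a fitted value would lean on the model form. They are not the standard errors of the planned regression.

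**The case against.** Several points on the other side have force.

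- **The aim is tentative.** The article says it will try to make an index and that prognostic models may be developed. A reader might infer a promise to tell GPs which women benefit; the text does not go that far.
- **The selection is a possibility.** A reader might infer that deferral will be mainly among milder women and that severe profiles will have very few or almost no untreated women. The article says only that milder women may be more likely to defer, and gives no rate. With high deferral and weak selection the number is respectable (about 57 above).
- **The calculation shows sparse overlap, not absent overlap,** and the article already admits limited subgroup power.
- **Safeguards are named:** adjustment for confounding by indication, and randomised trials to confirm any finding of no effect.
- **The reason is not empty.** The substudy asks whether women who recover without antibiotics can be identified at baseline, and data from milder women suit that question.
- **Overlap diagnostics usually belong in an analysis plan,** which is not shown here.

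The first three limit how strongly the point can be put. The rest do not remove it. Adjustment cannot create untreated severe women. Limited power concerns precision and says nothing of extrapolation; it also sits uneasily with an index for deciding who benefits, since that is itself a claim about differing effects. The trials are only a possibility, and the article expects ethical problems with them in severe cases, so a later correction is least likely there. Finally, the point does not rest on a missing diagnostic: it rests on a printed judgement and a printed intended use that do not match.

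**Conclusion.** The point holds in a limited form. The stated reason justifies conclusions in milder women only, and the stated use of the index is not confined to them. If deferral depends strongly on severity, estimates of the untreated course and of the antibiotic effect in severe cases would rest largely on the form of the model.

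The size cannot be settled from the article. Under the assumed inputs it ranges from serious (about 5 to 12 untreated severe women) to modest (about 57), depending on the overall deferral rate, the strength of selection and the share of severe cases. It is therefore not established that untreated severe women will be very few. That uncertainty is the argument for checking overlap before the index is applied to all profiles.

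The primary diagnostic objective is unaffected. For an exploratory substudy this is worth correcting, mainly because the correction is cheap.

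**What to change.** 1. Report the number and proportion of women who deferred, by baseline symptom severity.
2. Check the overlap of treated and deferring women, for example by comparing the distributions of the estimated probability of deferral in the two groups.
3. Limit antibiotic-effect and untreated-course estimates to the range of profiles in which both groups were observed, or label estimates outside it as extrapolation.
4. Reword the Background section on prognosis so that the index is said to estimate the 7-day course within that range, and claim to identify who benefits only if treatment-by-predictor terms support it.
5. In the Prognosis substudy, state that the reason for accepting selection applies to conclusions in milder women.

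The cost is some wording and one check on data already being collected. Recruitment and treatment are unchanged. The downside is a narrower stated domain for the index; if overlap turns out to be good, little or nothing is lost.
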